### Sample Size and Recruitment

Planned recruitment is approximately 1,300 patients. Recruitment is ongoing and will occur over 36 months. Enrollment began in March 2021.

To increase representativeness of selected sites, a large number of participating sites (up to 140) of different types (office- and hospital-based sites specialized in neurology), which are located geographically across Germany, are planned. To discourage physicians from selecting specific patients for inclusion in the study, they are instructed and trained to ask all eligible patients consecutively for their participation.

It is assumed that the persistence at year 5 will be 55% overall, including 50% of patients who switched to ozanimod treatment from another MS treatment and 55%−60% of treatment naive patients. A sample size of 1,331 patients is required to cover the estimated persistence rate of 0.55 with a 2-sided 95% confidence interval (CI) of 0.03 in each direction using the large sample normal approximation and after considering a dropout rate of 15%. This interval width is considered appropriate for correct description of the actual persistence rate on a descriptive level.

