**Methods:**

This prospective, noninterventional, postmarketing authorization study will enroll ~1,300 patients (≥18 years of age) with active RRMS. The decision to initiate ozanimod must have been made before and independent from study participation. Enrollment began in March 2021. Recruitment is ongoing and will last for 36 months across 140 sites in Germany. Treatment-naive patients or those having prior experience with a disease-modifying therapy receive oral ozanimod 0.92 mg/day after an initial dose escalation, per the summary of product characteristics recommendations, for up to 60 months. Persistence with ozanimod treatment (primary endpoint) is assessed at month 60. Secondary endpoints include additional physician-reported outcomes [persistence at earlier time points, annualized relapse rate, Expanded Disability Status Scale score, cognition (Symbol Digit Modalities Test), and incidence of adverse events], and patient-reported outcomes assessing patient satisfaction, adherence, and treatment modalities (Treatment Satisfaction Questionnaire for Medication, v1.4), disability (United Kingdom Neurological Disability Rating Scale), QoL (MSQOL-54 questionnaire), fatigue (Fatigue Scale for Motor and Cognitive Functions), and health economics [Work Productivity and Activity Impairment Questionnaire for Multiple Sclerosis (German v2.1); Multiple Sclerosis Health Resource Survey, v3.0]. A Multiple Sclerosis Documentation System with an internet-based e-health portal allows patients to view files and complete questionnaires. A safety follow-up will occur 3–8 months after the last ozanimod dose for patients who discontinue treatment early. Long-term results are anticipated after study completion in 2029. Yearly interim analyses are planned after enrollment has reached 25%.

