#### Statistical Methods

According to the non-interventional design of the study, the statistical analyses are descriptive and exploratory. No statistical hypotheses are formulated. There will be no inferential testing, and no *P* value will be provided. Summary statistics for continuous variables will include number of observations available and number of missing values, minimum, maximum, median, mean, and standard deviation. Summary statistics for discrete variables will be presented with counts and percentages and number of missing variables.

The analysis set for the primary analysis will comprise all patients who received at least 1 dose of ozanimod during the study and for whom at least 1 postbaseline documentation is available. A subgroup analysis will be performed examining pretreatment with disease-modifying therapies (i.e., patients who are treatment-naive compared with patients who switched from another disease-modifying therapy to ozanimod).

If a patient is lost to follow-up, efforts will be undertaken to collect the data from the previous visit. Data management procedures will be implemented to limit the amount of non-reported data. Analysis methods for handling missing data (e.g., last observation carried forward, imputation, or sensitivity analyses) will be applied.

Treatment (e.g., dosage, duration of treatment, dose modifications, treatment interruptions, and concomitant medications) will be analyzed descriptively.

The analysis of the primary endpoint of persistence rate over 60 months in routine clinical practice will be calculated descriptively as percentage value at 60 months (i.e., the proportion of patients who are on continuous treatment with ozanimod at this time point), including corresponding 95% CIs calculated by the Clopper-Pearson method. A patient will be classified as non-persistent if a medication gap > 90 days occurs before the end of the 60-month documentation period. A sensitivity analysis will be performed evaluating patients who are lost to follow-up as “non-persistent.” The persistence rate will be evaluated by Kaplan-Meier methods over the entire study period (patients who are lost to follow-up will be right-censored).

The analysis of persistence rate at months 12, 24, 36, and 48 (secondary endpoint) will be calculated descriptively and summarized as the proportion of patients on continuous treatment at the respective time point, with corresponding 95% CIs.

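### The sample size of 1,331 does not follow from its stated inputs, which give 1,244, and planned recruitment of about 1,300 matches neither number

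*Protocol article*

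**What the plan says.** All the sizing inputs stand in the Protocol article, section Sample Size and Recruitment:

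- Assumed rate: "It is assumed that the persistence at year 5 will be 55% overall".
- Precision: "with a 2-sided 95% confidence interval (CI) of 0.03 in each direction".
- Method: "using the large sample normal approximation".
- Attrition: "after considering a dropout rate of 15" per cent.
- Result: "A sample size of 1,331 patients is required to cover the estimated persistence rate of 0.55".

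The same section opens with a different number: "Planned recruitment is approximately 1,300 patients". The Methods paragraph of the abstract agrees with that one: the study "will enroll ~1,300 patients (≥18 years of age) with active RRMS".

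For the analysis of the primary endpoint, the Statistical Methods section specifies "95% CIs calculated by the Clopper-Pearson method", which is not the interval used for sizing.

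**The concern.** The study is descriptive and tests no hypothesis, so the width of the confidence interval for 60-month persistence is the only justification given for its size. The sentence that gives it supplies every input needed to repeat the sum, and the sum does not come out.

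Two smaller points add to this. The number called required (1,331) exceeds the number planned (about 1,300), so a literal reader would conclude that the study intends to under-recruit. And the sizing uses a narrower interval than the one to be reported, so the correct answer to the stated sum would not quite deliver the stated precision in the planned analysis.

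At stake is whether a reader can tell what precision the study was sized for, and whether 1,300 patients are enough.

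**Working it through.** **Inputs** (section Sample Size and Recruitment): p = 0.55; two-sided 95%, z = 1.96; half-width w = 0.03; normal approximation; dropout d = 0.15.

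**1. The plan's own calculation.** Evaluable n = z² p(1 − p) / w², rounded up; enrolled N = n / (1 − d), rounded up.

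- n = 1.96² × 0.55 × 0.45 / 0.03² = 1,056.4, so 1,057
- N = 1,057 / 0.85 = 1,243.5, so 1,244

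The printed figure is 1,331. The difference is 87 patients: 7.0% of 1,244, or 6.5% of 1,331.

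**2. Other conventions at ±0.03.** None gives 1,331.

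| Variant | Enrolled |
|---|---|
| Dropout applied as n × 1.15 | 1,216 |
| p = 0.50 | 1,257 |
| Continuity correction (1,090 evaluable) | 1,283 |
| Clopper-Pearson (1,097 evaluable) | 1,291 |
| z rounded to 2 (1,100 evaluable) | 1,295 |
| 90% confidence | about 876 |
| 99% confidence | about 2,147 |
| Dropout applied twice | 1,463 |

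**3. What does give 1,331.**

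- Half-width 0.029, all else as stated: 1.96² × 0.55 × 0.45 / 0.029² = 1,130.5, so 1,131; 1,131 / 0.85 = 1,330.6, so 1,331. This is exact.
- Half-width kept at 0.03: 1 − 1,057 / 1,331 = 0.206, so dropout would have to be 20.6% rather than 15%.
- Also, 1,131 × 1.15 = 1,300.7. The target of about 1,300 could therefore come from the same 0.029 with dropout multiplied on instead of divided out. This is a conjecture; the article does not say so.

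**4. Precision at each enrolment, after 15% dropout.** The normal half-width is 1.96 × √(0.2475 / n). For Clopper-Pearson, x = 0.55n rounded to a whole number; the lower limit is the 0.025 quantile of Beta(x, n − x + 1) and the upper limit is the 0.975 quantile of Beta(x + 1, n − x). The table gives distances from x / n.

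| Enrolled | Evaluable | Normal | Clopper-Pearson |
|---|---|---|---|
| 1,244 | 1,057 | ±0.0300 | −0.0306 / +0.0303 |
| 1,291 | 1,097 | not needed | −0.0300 / +0.0297 |
| 1,300 | 1,105 | ±0.0293 | −0.0299 / +0.0296 |
| 1,331 | 1,131 | ±0.0290 | −0.0295 / +0.0293 |

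The value 1,097 is the smallest evaluable number at which both Clopper-Pearson arms are within 0.03 and stay there for the next 19 values of n. The enrolment is 1,097 / 0.85 = 1,290.6, so 1,291.

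**The case against.** The strongest defence is that nothing was miscalculated. A half-width of 0.029 gives exactly 1,331 and prints as 0.03 to two decimals, so a condensed article may simply have rounded its precision. That is the likeliest explanation, but it remains an inference. As printed, the sentence pairs 0.03 with a number that 0.03 does not produce.

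Second, the planned number is given as approximate. A gap of 31 in 1,331 is 2.3%, and 1,331 rounds to 1,300 at the nearest hundred. This is fair. On its own the gap would not merit comment; it matters only because 1,331 is called required.

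Third, sizing on a normal approximation and reporting an exact interval is a legitimate choice that the article makes openly, and the miss at 1,057 evaluable is only about 0.0006. This also stands: it is a mismatch and not a contradiction. It bears on the remedy, because simply replacing 1,331 with 1,244 would leave the reported interval slightly wider than ±0.03.

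Fourth, the discrepancy is conservative. Both 1,300 and 1,331 exceed 1,244, and both meet ±0.03 under either interval. This is correct and limits the finding to the stated justification. It does not make the stated number right.

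**Conclusion.** The concern holds. From the stated inputs the required enrolment is 1,244, not 1,331, an overstatement of 87 patients. The planned figure of about 1,300 equals neither and lies 31 below the one called required.

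There is no shortfall in precision. With 1,300 enrolled and 15% dropout, the planned Clopper-Pearson interval stays within ±0.03 at a persistence of 0.55. The ambiguity over the intended half-width is 0.029 against 0.030. What needs correcting is the sample-size statement; recruitment can stay as it is.

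This rests on reading the 15% as patients lost from the denominator of the primary proportion, which is how a dropout inflation is normally meant, and on the stated 0.55. That the authors used 0.029 is probable but not documented.

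**What to change.** Restate the sizing on the interval that will be reported. For example: for a two-sided 95% Clopper-Pearson interval within ±0.03 at an assumed persistence of 0.55, 1,097 evaluable patients are needed; allowing for 15% dropout, 1,291; about 1,300 will be enrolled. This removes the wrong number, matches sizing to analysis and supports the present target.

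If the authors prefer to keep 1,331 and the normal approximation, they should print the half-width as 0.029 and describe about 1,300 as a rounded target that gives ±0.0293. Raising recruitment to 1,331 is not needed to meet ±0.03.

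Either way the cost is a text correction, with no change to recruitment, data collection or analysis.

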### Data Collection, Management, and Analysis

#### Data Collection Methods

As part of routine care, the study physician or qualified study staff members at the study site enter data on treatment, MS relapses, EDSS, SDMT, and AEs since the patient's last visit, according to the timeline outlined in Table 2, using an electronic case report form (eCRF; Figure 3). Laboratory panels and MRIs are performed only as available based on routine clinical assessments at each study center.

**Figure 3 F3:**
[figure not shown]
Architecture and data flow within OzEAN eCRF and OzEAN patient portal. Physician-reported assessments are performed at the study site, and data are entered by physicians into the OzEAN eCRF. Patient-reported assessments are completed by patients using the OzEAN patient portal, and data are fed into the OzEAN eCRF. The patient portal interface additionally provides a calendar, medication plan, documents module, and access to surveys (PROs). Data from the OzEAN eCRF are transmitted to Winicker Norimed GmbH (the contract research organization) for storage on secure servers. Data on adverse events are additionally transmitted to the sponsor or its designee as part of standard safety reporting. CRO, contract research organization; eCRF, electronic case report form; PRO, patient-reported outcome.

PROs (including adherence, TSQM v1.4, UKNDS, MSQOL-54, FSMC, WPAI-MS v2.1, and MS-HRS v3.0), preferably scored directly by the patient, are collected via the Multiple Sclerosis Documentation System 3D [MSDS^3D^ (24, 25)] with a study-specific, internet-based, patient e-health portal (Figure 3) according to the timeline in Table 2. The patient portal is accessible via computer or tablet and allows patients to download files and complete questionnaires (Figure 4). Alternatively, upon patient request, PROs are provided as paper-based versions to be completed and scored at the study site. All PRO questionnaires are made available in the German language. A detailed description of the instruments used in these assessments is available in Table 4.

**Figure 4 F4:**
[figure not shown]
OzEAN patient portal user interface. On the start page of the patient user interface, the patient can select from the following options: surveys (PROs), questions about medication intake (medication plan), documents for download, and calendar. The medication plan displays information on ozanimod treatment. The documents module provides downloadable files (e.g., patient portal user manual and ozanimod SmPC). The calendar displays the patient's start date and participation within the OzEAN study and is equipped with a reminder to take ozanimod. The patient is also able to review and visualize personal longitudinal data graphically. PRO, patient-reported outcome; SmPC, Summary of Product Characteristics.

**Table 4 T4:** Description of Measures in OzEAN.

**Physician-Reported Assessment**	
Expanded Disability Status Scale (EDSS) (10)	The EDSS is a standardized, widely accepted method to evaluate disability in people with MS. Severity of disability in multiple functional systems (pyramidal, cerebellar, brain stem, sensory, bowel and bladder, visual or optic, cerebral or mental, and other) observed during a standard neurological examination is scored on a numerical scale ranging from 0 (normal) to 10 (death due to MS).
Symbol Digit Modalities Test (SDMT) (12, 13)	The SDMT is a reliable measure of change in cognitive processing speed over time. Patients are given a key showing numbers [0–9] paired with symbols. They are also presented with rows of the same symbols (in random order) and are asked to provide the matching numbers, based on the key. The score is based on the number of correct responses within 90 s, with higher scores indicating better performance. The SDMT has been validated in patients with MS and is typically administered orally in this population. Changes in SDMT raw score of ≥ 4 points or 10% are considered clinically meaningful.
**Patient-Reported Assessment**	
Treatment Satisfaction Questionnaire for Medication, version 1.4 (TSQM v1.4) (14, 15)	The TSQM v1.4 is a general measure of treatment satisfaction with medication in chronic diseases that has been tested extensively in people with RRMS. It comprises 14 items covering 4 domains: effectiveness, side effects, convenience, and global satisfaction. On individual items, patients rate their satisfaction with a medication, presence/absence and bothersomeness of side effects, extent to which side effects interfere with functioning and impact treatment satisfaction, ease of use and convenience, and confidence in the treatment. Ratings reflect experience with the medication over the previous 2–3 weeks, or since the patient's last use of the medication. Scores range from 0 to 100, with higher scores representing greater satisfaction.
United Kingdom Neurological Disability Rating Scale (UKNDS) (16, 17)	The UKNDS is a simple, user-friendly clinical disability scale that is valid and reliable for the assessment of patients with MS. It is derived from Guy's Neurology Disability Scale and consists of 11 domains: cognition, mood, vision, speech, swallowing, upper limb function, lower limb function, bladder function, bowel function, fatigue, and pain. Each subscale is scored on a 6-point Likert scale ranging from 0 (normal) to 5 (total loss of function/maximum impairment), producing an overall sum score ranging from 0 (best) to 55 (worst). Improvement or worsening of at least 1 grade in each subscale are considered clinically meaningful.
Multiple Sclerosis Quality of Life-54 (MSQOL-54) (18)	The MSQOL-54 is a multidimensional health-related QoL measure that combines both generic and MS-specific items into a single instrument. The generic component is the Short Form-36 Health Survey (SF-36) (42), to which 18 items were added to identify MS-specific issues. There are 54 items distributed into 12 subscales (physical function, role limitations-physical, role limitations-emotional, pain, emotional well-being, energy, health perceptions, social function, cognitive function, health distress, overall quality of life, and sexual function), along with 2 summary scores (physical composite summary [PCS] and mental health composite summary [MCS]). A change in score equivalent to 0.5 SD has been found to have almost universal relevance as a minimum clinically important difference for health-related QoL. Using the 0.5 SD threshold for the SF-36, a change of ≥ 5 points in PCS and MCS has been proposed to be clinically meaningful (23).
Fatigue Scale for Motor and Cognitive Functions (FSMC) (19)	The FSMC includes a cognitive scale and a physical (motor) scale, each consisting of 10 items. Items are scored using a 5-point scale ranging from 1 to 5, yielding a total score range of 20 (no fatigue at all) to 100 (severest grade of fatigue). Based on cut-off values for severity categories, a change from baseline of ≥ 10 in FSMC sum score, ≥ 6 in cognitive subscore, and ≥ 5 in physical subscore should denote a clinically meaningful change.
Work Productivity and Activity Impairment Questionnaire for Multiple Sclerosis (WPAI-MS v2.1) (20)	The WPAI-MS German v2.1 consists of 6 items across 4 domains: absenteeism (work time missed), presenteeism (impairment at work/reduced on-the-job effectiveness), work productivity loss (overall work impairment/absenteeism + presenteeism), and activity impairment. Each domain is measured on a scale of 0% to 100% impairment. The recall period is 7 days. A lower score on the WPAI-MS v2.1 subscales indicates less impairment (i.e., an improvement).
Multiple Sclerosis Health Resource Survey (MS-HRS v3.0) (21)	The MS-HRS v3.0 is a validated, 24-item questionnaire that enables a holistic and longitudinal examination of resource use and costs (direct medical, direct non-medical, and indirect) in patients with MS. It documents social resource use, independent of source of reimbursement, and economic impact on work, family, and leisure. The instrument allows for allocation of a monetary value to a specific disease state, to an event (e.g., a relapse), or to a specific therapy.

*MS, multiple sclerosis; QoL, quality of life; RRMS, relapsing-remitting multiple sclerosis; SD, standard deviation*.

AEs elicited as part of PRO data collection are subject to AE reporting. Investigators must review responses provided by patients to PRO instrument questions that assess safety to determine if AE reporting is warranted. The physician will enter AE data into the eCRF.

In the safety follow-up visit for patients withdrawn from the observational study before month 60, safety-related data (AEs) and data on any subsequent MS treatment and concomitant medication are collected in addition to PROs.

#### Data Management

Documentation of study data by physicians and authorized site staff is done exclusively online using the eCRF. The data are transmitted via secure connections and stored on secure servers of MedicalSyn GmbH, the eCRF, data management, and patient portal provider. Data entries in the patient portal are checked for plausibility and accuracy using validation programs, which generate automated queries. Open queries are displayed in the current status overview to be resolved. Data management screens new or updated free text entries in the patient portal for hidden AEs. The system follows open queries on a regular basis and communicates queries to the site. The site responds to open queries online.

#### Statistical Methods

According to the non-interventional design of the study, the statistical analyses are descriptive and exploratory. No statistical hypotheses are formulated. There will be no inferential testing, and no *P* value will be provided. Summary statistics for continuous variables will include number of observations available and number of missing values, minimum, maximum, median, mean, and standard deviation. Summary statistics for discrete variables will be presented with counts and percentages and number of missing variables.

The analysis set for the primary analysis will comprise all patients who received at least 1 dose of ozanimod during the study and for whom at least 1 postbaseline documentation is available. A subgroup analysis will be performed examining pretreatment with disease-modifying therapies (i.e., patients who are treatment-naive compared with patients who switched from another disease-modifying therapy to ozanimod).

If a patient is lost to follow-up, efforts will be undertaken to collect the data from the previous visit. Data management procedures will be implemented to limit the amount of non-reported data. Analysis methods for handling missing data (e.g., last observation carried forward, imputation, or sensitivity analyses) will be applied.

Treatment (e.g., dosage, duration of treatment, dose modifications, treatment interruptions, and concomitant medications) will be analyzed descriptively.

The analysis of the primary endpoint of persistence rate over 60 months in routine clinical practice will be calculated descriptively as percentage value at 60 months (i.e., the proportion of patients who are on continuous treatment with ozanimod at this time point), including corresponding 95% CIs calculated by the Clopper-Pearson method. A patient will be classified as non-persistent if a medication gap > 90 days occurs before the end of the 60-month documentation period. A sensitivity analysis will be performed evaluating patients who are lost to follow-up as “non-persistent.” The persistence rate will be evaluated by Kaplan-Meier methods over the entire study period (patients who are lost to follow-up will be right-censored).

The analysis of persistence rate at months 12, 24, 36, and 48 (secondary endpoint) will be calculated descriptively and summarized as the proportion of patients on continuous treatment at the respective time point, with corresponding 95% CIs.

Medication adherence (secondary endpoint) will be evaluated categorically in terms of the percentage of doses taken as prescribed.

Secondary endpoints of clinical effectiveness (ARR, EDSS, and SDMT) and all PRO measures (changes from baseline, including proportion of patients who achieved a clinically meaningful change from baseline) will be analyzed descriptively. For TSQM v1.4, it is assumed that a clinically meaningful relationship between TSQM v1.4 domains and clinical outcomes is given if the effect size (Cohen's d) is > 0.3 (15).

All AE data will be listed and summarized. AEs will be classified using the Medical Dictionary for Regulatory Activities (MedDRA) classification system. The incidences based on the patient population enrolled as well as incidence density rates (number of events/sum of person-time in years) of all AEs, serious AEs (SAEs), adverse drug reactions (ADRs), and serious ADRs will be summarized by system organ class, preferred term, and relationship to study treatment. AEs leading to discontinuation from treatment will also be summarized and listed separately.

SAS software version 9.2 or higher will be used for analyses.

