**Safety assessment**						
AEs/SAEs	Assessed continuously throughout study					
Laboratory panel^h^	X^h^	X^h^	X^h^	X^h^		X^h^

*AE, adverse event; ARR, annualized relapse rate; EDSS, Expanded Disability Status Scale; FSMC, Fatigue Scale for Motor and Cognitive Functions; MRI, magnetic resonance imaging; MS, multiple sclerosis; MSFC, Multiple Sclerosis Functional Composite; MS-HRS v3.0, Multiple Sclerosis Health Resource Survey, version 3.0; MSQOL-54, Multiple Sclerosis Quality of Life-54; SAE, serious adverse event; SDMT, Symbol Digit Modalities Test; TSQM v1.4, Treatment Satisfaction Questionnaire for Medication, version 1.4; UKNDS, United Kingdom Neurological Disability Rating Scale; WPAI-MS v2.1, Work Productivity and Activity Impairment Questionnaire for Multiple Sclerosis, version 2.1*.

a *Documentation performed directly after a patient reached the regular end of study (at month 60) or permanently discontinued ozanimod treatment before month 60; if routine data were collected that do not meet any of the documentation time points offered, these data may be entered with the month 60 documentation*.

b *Follow-up documentation of potential AEs and subsequent therapy, performed approximately 3–8 months after stopping treatment with ozanimod and when a new MS therapy is initiated, or after 8 months (at the latest) if there is no subsequent MS therapy initiated*.

c *Includes MS diagnosis according to International Classification of Diseases, Tenth Revision; first manifestation of MS; course of MS disease and number of relapses within the year before enrollment; and type and duration of prior disease-modifying therapies for MS*.

d *Includes vital parameters, physical status*.

e *Treatment modalities referring to ozanimod, including (planned) date of first administration of ozanimod, reason for switch to ozanimod, interruptions, re-initiation of therapy following treatment interruption, and reason for discontinuation in case of switch to another MS treatment*.

f *At yearly intervals (months 12, 24, 36, 48, and 60) only*.

g *At 6-month intervals (months 6, 12, 18, and 24) only*.

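### The primary persistence set leaves out dosed patients with no post-baseline record, so the analysis counting lost patients as non-persistent is not a true worst case if run in that set

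*Protocol article*

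**What the plan says.** All of the analysis rules are in the Protocol article, Statistical Methods.

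- **Set.** The primary analysis comprises "all patients who received at least 1 dose of ozanimod during the study and for whom at least 1 postbaseline documentation is available".
- **Primary proportion.** It is "the proportion of patients who are on continuous treatment with ozanimod at this time point", evaluated at month 60 with a Clopper-Pearson 95% interval.
- **Non-persistence.** "A patient will be classified as non-persistent if a medication gap > 90 days occurs before the end of the 60-month documentation period".
- **Sensitivity analysis.** "A sensitivity analysis will be performed evaluating patients who are lost to follow-up as" non-persistent. No separate set is named for it.
- **Missing data in general.** "Analysis methods for handling missing data (e.g., last observation carried forward, imputation, or sensitivity analyses) will be applied". The text does not say how a lost patient enters the primary proportion.

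Two other places bear on who is excluded. Table 2, footnote a, describes the end-of-observation form: "Documentation performed directly after a patient reached the regular end of study (at month 60) or permanently discontinued ozanimod treatment before month 60". Study Setting and Treatment adds a safety follow-up for patients who stop early.

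**The concern.** The endpoint is staying on treatment from baseline, yet entry to its denominator depends on something that happens after treatment starts, namely that a later record exists. The dose condition already removes untreated patients. What the second condition removes is dosed patients about whom nothing more is known.

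For a change-from-baseline endpoint this is reasonable, because no change can be computed without a later value. Persistence differs. Under the rule that lost means non-persistent, a patient with no later record can be classified without any further measurement.

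At stake is mainly the sensitivity analysis. A reader will take it as the lower bound on persistence, and the Discussion lists prespecified handling of lost patients among the measures against attrition bias. A bound that leaves out patients lost before any later record is not a full bound.

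**Working it through.** **Inputs.** From Sample Size and Recruitment: expected 5-year persistence 0.55, half-width 0.03, dropout 15%, required sample 1,331. The share *f* of dosed patients with no post-baseline record is not in the document and is an assumption throughout.

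**The plan's own figure.** n = 1.96² × 0.55 × 0.45 / 0.03² = 1,056.4, so 1,057; 1,057/0.85 gives 1,244, not 1,331. A half-width of 0.029 gives 1,131, and 1,131/0.85 gives 1,331. This is a separate matter. Here 0.03 serves only as a yardstick, and 1,331 only turns shares into patient counts.

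**Step 1: who leaves the set.** The criterion is any documentation, not a completed visit. A patient who stops early and has the end-of-observation form or the safety follow-up has a post-baseline record, stays in, and counts as non-persistent. Only dosed patients with no record at all after baseline leave.

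**Step 2: general effect on a proportion.** Let *r* be persistence in the restricted set and *q* the persistence, true or assigned, of those excluded. The all-dosed rate is (1 − f)·r + f·q, so the restricted set differs from it by f·(r − q). The rate is inflated only if q < r.

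**Step 3: sensitivity analysis.** Patients with no later record are lost to follow-up, so its rule sets q = 0. The difference is f·r, which is positive whenever f > 0. As an illustration, assume that the 15% dropout is all loss to follow-up and that persistence among the rest is 55%. The all-dosed rate is 0.85 × 0.55 = 46.75%. If a share *s* of the lost patients has no later record, the restricted set reports 0.4675/(1 − 0.15s):

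| s | Restricted rate | Excess (points) |
|---|---|---|
| 10% | 47.5% | +0.7 |
| 20% | 48.2% | +1.4 |
| 50% | 50.5% | +3.8 |
| 100% | 55.0% | +8.3 |

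The last row is the limiting case, in which the sensitivity analysis corrects nothing.

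**Step 4: primary proportion, if the excluded patients are all non-persistent.** With a true all-dosed rate of 0.55 and q = 0, the reported rate is 0.55/(1 − f):

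| f | Reported | Excess (points) |
|---|---|---|
| 1% | 55.6% | +0.6 |
| 2% | 56.1% | +1.1 |
| 3% | 56.7% | +1.7 |
| 5% | 57.9% | +2.9 |

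The excess equals 3 points when 0.55/(1 − f) = 0.58, so f = 1 − 0.55/0.58 = 5.2%, about 69 of 1,331.

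**Step 5: primary proportion under other rules.** If lost patients are left out of the primary proportion in any case, the set condition changes nothing. If last observation carried forward, one of the listed examples, kept them as persistent (q = 1), exclusion would lower the rate. With f = 2% and r = 0.55, the all-dosed rate would be 0.98 × 0.55 + 0.02 = 55.9%, against 55.0% in the restricted set.

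**The case against.** The strongest reply is that the excluded group may be very small. Any record keeps a patient in. Persistence and adverse events are recorded continuously, adverse events also reach the study through the patient portal, and the plan commits to efforts to retrieve data on lost patients. Table 1 bars patients already on ozanimod, and Table 2, footnote e, allows the baseline form to carry a planned start date. Confirming that a first dose was taken will therefore often need a later record, so the two conditions overlap. This stands, and it is why the size cannot be fixed from the document. It does not remove the gap.

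A second reply is that an article may leave the set for a sensitivity analysis to the full plan. That is fair, and the point is conditional for that reason. But the primary set itself is stated outright, and no other set is named for persistence.

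A reader might infer three stronger claims that the document does not support:

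- *That the earliest dropouts as a whole are removed.* Documented early discontinuers remain and count against persistence.
- *That the primary result is necessarily inflated.* The rule for lost patients in the primary proportion is not stated, and Step 5 shows that the effect could be zero or negative.
- *That the other persistence or safety analyses are also affected.* In the Kaplan-Meier analysis "patients who are lost to follow-up will be right-censored", so these patients would be censored near time zero and add almost nothing. A broader population for adverse event incidence is ordinary practice.

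**Conclusion.** The point holds in a narrow form. Conditioning the persistence denominator on a post-baseline record serves no purpose for this endpoint. If the sensitivity analysis uses that set, its rate is biased upward whenever a dosed patient has no later record. The direction is certain there; the size is not.

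For the primary proportion, inflation requires that the excluded patients are less persistent than the rest or would be counted as non-persistent. If all are non-persistent, an assumed exclusion of 1% to 5% moves a true 55.0% to between 55.6% and 57.9%. Reaching the planned half-width would take about 5.2% of dosed patients, roughly a third of the whole 15% dropout allowance, lost without a single record. The study is descriptive and no test depends on the result, so this is a worthwhile, inexpensive improvement and not a threat to the study.

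**What to change.** For persistence, define the denominator as all enrolled patients who received at least one dose. At minimum, do this in the analysis that treats lost patients as non-persistent, and count patients with no later record as non-persistent there. Report how many dosed patients have no post-baseline documentation, so that a reader can judge the effect. Keep the post-baseline condition for the change-from-baseline endpoints.

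The cost is one sentence in the analysis-set definition and no new data. The downside is a slightly lower reported persistence; if no dosed patient lacks a later record, the result is unchanged.
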